### Sample and Eligibility

Potential participants from the county of Nottinghamshire will be able to self-refer, and their eligibility will be assessed by an automated digital program on the study website. The study website requests GP practice contact details in case the participant is ineligible for the study.

The inclusion criteria are as follows:

Aged 16 years or overResident in the County of NottinghamshireScores between 10 and 20 on the 9-item Personal Health Questionnaire (PHQ-9) [25] and/or 10 or more on the 7-item Generalized Anxiety Disorder (GAD-7) questionnaire [26], indicating probable caseness for depression and anxiety, respectively, but not a definite diagnosis of depression or anxiety disorderAccess to the Internet through a computer, tablet, or smartphone (Windows, iPhone operating system [iOS, Apple Inc], and Android)Able and willing to give informed consent (through electronic consent)

The exclusion criteria are as follows:

Scores 21 or more on the 9-item Personal Health Questionnaire (PHQ-9, severe depression)Scores 2 or 3 on PHQ-9 item “thoughts that you would be better off dead or of hurting yourself in some way.”Scores below 10 on PHQ-9 and 7-item Generalized Anxiety Disorder (GAD-7) questionnaireBWW and Moodzone are only available in English. Therefore, the website will recommend to participants that if they do not feel that they are sufficiently proficient in the use of the English language, they need not take part. There will be no test of proficiency.

Participants who are ineligible for the trial because they score in the severe range on the PHQ-9 or signs of suicidality will be provided with an opportunity to request that the study team inform their GP, mental health care team, or carer of their current mood state. If they choose not to take this offer, the study team will follow this up on one occasion with an email to ask them again if they would like the team to inform their GP or care team. If they do not reply, the team will consider this confirmation that they do not wish us to act on their behalf.

Participants that are under age will be given details of local children’s mental health services. They will be informed that they may return to the study website if they turn 16 years within the recruitment period, should they still wish to participate.

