### Expected Duration of Participant Participation

Participation in the study will be for 6 months (see Figure 1 for participant journey through the study). Participants will receive electronic follow-up invitations at 3, 6, 12, and 26 weeks after randomization to be completed on the website. Participants may also be asked to take part in a short interview by phone or face-to-face to talk about their experiences of services and/or the study no later than 3 months from the ending of their participation.

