#### Secondary Outcomes Measures

Maintenance of well-being 12 and 26 weeks using the WEMWBSGAD-7 scale—completed as part of eligibility at baseline and then at 3, 6, 12, and 26 weeks as a brief measure of the severity of 7 symptoms of anxietyPHQ-9—completed as part of eligibility at baseline and then at 3, 6, 12, and 26 weeks as a measure of depression severity according to the *Diagnostic Statistical Manual, 4th edition* criteria [27]12-item Medical Outcomes Study Short Form health survey version 2.0 (SF-12v2) [28]—a short and practical measure of health-related QOL derived from the longer SF36 that is obtained during interviewSocial support is measured using the 8-item Medical Outcomes Study Social Support Survey (MOS-SS) [29], and it is completed at baselineSocial function on the 8-item Work and Social Adjustment Scale (WSAS) [30]—a simple measure of impact on function, which is attributable to a particular cause such as depression or anxiety. It is completed at baseline and then at 3, 6, 12, and 26 weeks

Mediators of the effectiveness of BWW compared with Moodzone on mental well-being might be the emotional and informational support subscales of the MOS-SS [29]. Data collected by BWW suggest that perceived social support might be an important mediator of outcome, particularly in people experiencing life events and loneliness.

Moderators of outcome at baseline might be the presence of life events in the previous 6 months, measured by the 12-item Brugha Inventory of Life Events [31], and the presence of anxiety alone at baseline. Personality dysfunction will be measured at baseline using the 8-item Standardised Assessment of Personality-Abbreviated Scale (SAPAS) [32]. There may be an interaction between the presence of life events at baseline and greater perceived emotional support from BWW at 3 months and on mental well-being at 6 months, whereas higher scores on the SAPAS may predict dropout and little difference between the treatment arms on mental well-being at 6 weeks.

**Table 1 table1:** Timing and delivery of outcome measures.

Measure	Baseline	3 weeks	6 weeks	12 weeks	26 weeks
WEMWBS^a^	Website	Website	Website	Website	Website
PHQ-9^b^	Website	Website	Website	Website	Website
GAD-7^c^	Website	Website	Website	Website	Website
WSAS^d^	Website	Website	Website	Website	Website
MOS-SS^e^	Website	X^f^	X	X	X
SAPAS^g^	Website	X	X	X	X
Brugha Life^h^	Website	X	X	X	X
SF12-v2^i^	Website	X	X	X	Interview
CSRI^j^	Website	X	X	X	Interview

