### Randomization and Monitoring

The treatment to which a participant is assigned will be determined by a computer-generated pseudorandom code using random permuted blocks of varying size by a randomization system embedded within the website. No stratification or minimization is required. The outcome will be single-blind with the clinical trials manager and research associates responsible for the collection, cleaning, and analysis of the data remaining blind to arm allocation until data collection has been completed. Cases of unblinding will be recorded electronically but will not be excluded. Unblinding will only be necessary upon completion of data collection.

Overall, trial monitoring and oversight will be carried out by the CLAHRC-EM Scientific Committee who will act as the trial steering committee and data monitoring committee. The CLAHRC-EM scientific committee is composed of independent experts in statistics, epidemiology, medicine, and patient and public involvement. They will be sent quarterly reports on the status of the study and have the power to recommend or implement changes to the protocol if necessary. They are also able to stop the study if it is deemed unsafe or is failing to recruit after all avenues to recruitment have been exhausted.

There is no planned assessment of safety within the study design, and unless participants report any intercurrent illness or adverse events directly to the study team, it is unlikely that these can be recorded systematically.

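### The committee may stop the trial as unsafe, but no safety assessment is planned and no safety use of the PHQ-9 collected after randomisation is stated

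*Protocol article*

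**What the plan says.** The relevant statements are spread over four sections of the protocol article.

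- **Power to stop** (Randomization and Monitoring). The scientific committee is the body "who will act as the trial steering committee and data monitoring committee". Of its members the article says: "They are also able to stop the study if it is deemed unsafe".
- **What the committee receives** (same section). "They will be sent quarterly reports on the status of the study". No safety content is named.
- **Safety assessment** (next paragraph). On the capture of events the article says: "unless participants report any intercurrent illness or adverse events directly to the study team, it is unlikely that these can be recorded systematically". The opening of that sentence is plainer still: "There is no planned assessment of safety within the study design".
- **PHQ-9 after randomisation** (Secondary Outcomes Measures and Table 1). The PHQ-9 is "completed as part of eligibility at baseline and then at 3, 6, 12, and 26 weeks as a measure of depression severity". The section on expected duration of participation agrees: "Participants will receive electronic follow-up invitations at 3, 6, 12, and 26 weeks after randomization".
- **PHQ-9 at entry** (Sample and Eligibility). A total of 21 or more excludes, and so does the self-harm item: "Scores 2 or 3 on PHQ-9 item". Action on such scores is described only for people found ineligible at screening.
- **Blinding** (Randomization and Monitoring; Statistical Analysis). The trials manager and research associates stay blind to arm until data collection ends, and the trial statistician is also blind.

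**The concern.** The section gives a committee the power to act on harm and, one paragraph later, says that evidence of harm will not be assembled on any planned or systematic basis. This is an affirmative statement about the design, so it is not a detail that an unseen analysis plan would normally supply. An analysis plan also governs the final analysis more than what a committee sees each quarter.

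The reason given, that adverse events reach the team only if participants volunteer them, does not apply to a questionnaire scheduled four times and stored on the trial website. The plan treats a severe total or a raised self-harm item as important enough to keep people out of the trial, but describes no look at whether randomised participants reach the same levels.

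At stake is the trial's ability to notice, during follow-up or at its end, that more people in one arm reach those levels. A difference in mean scores need not show this, because an average improvement can coexist with worsening in a minority.

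**Working it through.** The plan offers no safety figure to reproduce. The main check sets the statements side by side; the arithmetic only shows how much data exist and how far they could go.

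**1. The two statements.** The committee can stop the study if it is deemed unsafe. No safety assessment is planned. The two can stand together only if the judgement rests on something unplanned. What the article leaves is spontaneous reports and status reports of unspecified content. Because the data team and the statistician are blind, no route is described by which by-arm information would reach the committee during the trial.

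**2. Data already collected.** There are 4 PHQ-9 time points after randomisation (weeks 3, 6, 12, 26). The plan needs 676 evaluable participants and allows for 50% loss: 676 / (1 − 0.5) = 1352, as stated. Follow-up forms number at most 1352 × 4 = 5408, or 676 × 4 = 2704 if only 676 people complete every visit and the rest complete none.

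**3. Interpretability.** A total of 21 or more and an item score of 2 or 3 are both entry exclusions, and the eligibility PHQ-9 is also the baseline measure. Both counts are therefore zero in each arm at baseline, so anyone counted at follow-up has moved to that level since entry.

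**4. What a by-arm comparison could detect.** The documents give no crossing rates, so these are assumptions. With h = 2·arcsin(√p₂) − 2·arcsin(√p₁) and power ≈ Φ(h·√(n/2) − 1.96):

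- 5% against 10%: h = 0.6435 − 0.4510 = 0.1925
- 10% against 17%: h = 0.8500 − 0.6435 = 0.2065

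| Responders per arm | 5% vs 10% | 10% vs 17% |
|---|---|---|
| 338 (full evaluable sample) | 71% | 77% |
| 169 (half) | 42% | 48% |
| 84 (about a quarter) | 24% | 27% |

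At the full sample, differences of this size would be reasonably detectable. At the sizes a quarterly report would hold during recruitment, they would mostly not be.

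**5. Effect of dropout.** Take 1352 / 2 = 676 randomised per arm, with assumed true crossing rates of 5% and 10%. If everyone responds at the planned 50%, the table shows 5% and 10%. Suppose instead that, in the 10% arm only, people who cross respond at half that rate (25%, an assumption):

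- 10% arm: 67.6 × 0.25 = 16.9 crossers among 16.9 + 608.4 × 0.5 = 321.1 responders, or 5.3%
- 5% arm: 33.8 × 0.5 = 16.9 crossers among 338 responders, or 5.0%

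The doubling disappears from the table, while overall response differs only modestly (321.1 / 676 = 47.5% against 50%). Denominators by arm are therefore necessary, but they do not remove the risk of false reassurance.

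**The case against.** The best case for the plan runs as follows. A general power to stop an unsafe study can coexist with no scheduled safety assessment, and the committee could act on events reported directly to the team. The omission is stated openly, in a trial with ethics approval that excludes severe and at-risk people at entry and tests a professionally staffed service. Report contents often sit in a full protocol or a committee charter, which an article condenses. Interviews will also ask about negative experiences.

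Much of this stands, and it limits what can be said. Three stronger readings are tempting, and the document does not support them:

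- *That the stopping power cannot be used at all.* Spontaneous reports remain possible. The accurate statement is that no planned or systematic assessment supports it.
- *That the PHQ-9 will be analysed only as mean severity.* The Statistical Analysis section summarises outcomes by arm over follow-up, allows medians and frequencies as well as means, and defers details to an analysis plan that is not shown. Threshold counts may or may not appear there.
- *That the trial undertakes to show the service is safe.* The word occurs in the abstract's background as motivation. Safety is not among the stated objectives.

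What the objection does not remove is the plain statement that no safety assessment is planned, beside a power to stop for safety and a scheduled instrument that the plan itself treats as a marker of risk. Interviews reach a selected sample and are not described as an input to the committee.

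**Conclusion.** The concern holds in a limited form. The article gives a stop-for-safety power, says that no safety assessment is planned, and names no safety use of PHQ-9 data that the website will already hold at four follow-ups. The two statements should be reconciled. This does not touch the primary estimate, the sample size or the main analysis; it is a low-cost gain in the trial's capacity to notice harm.

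The size cannot be given as a bias or an error rate. The 71% and 77% power figures rest on assumed crossing rates and on all 338 evaluable responders per arm. They describe a final table. At 84 to 169 responders per arm, power on the same assumptions is roughly 24% to 48%, so interim tables would be descriptive only. The conclusion itself depends on none of these rates.

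**What to change.** Amend the Randomization and Monitoring section so that the two statements agree, by saying what information the committee sees, by arm, and how often. Add one descriptive table to the quarterly committee report and repeat it in the final report. By coded arm and at weeks 3, 6, 12 and 26, it would show:

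- the numbers randomised, due for that follow-up and responding;
- the number and percentage of responders with a PHQ-9 total of 21 or more;
- the number and percentage of responders with a self-harm item score of 2 or 3.

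These are the plan's own entry-exclusion levels, used here for reporting only. No clinical action rule or stopping boundary is proposed.

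A fall of 3 points or more on the WEMWBS should not be added as a harm indicator. The plan uses 3 points as a between-group difference. With its own means and SDs (42.20, SD 9.83 at baseline; 44.46 and 41.46, SD 12.0 at 6 weeks), normality and a pre-post correlation of 0 to 0.7, the SD of change is √(9.83² + 12² − 2r·9.83·12) = 15.5 to 8.7. Then Φ((−3 − 2.26)/SD) flags 37% to 27% of the Big White Wall arm and Φ((−3 + 0.74)/SD) flags 44% to 40% of the Moodzone arm, even if the intervention works as planned. That would mostly restate the primary outcome and its variability.

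Costs: a modest programming and reporting task; someone outside the blinded trial team must hold the arm codes; power is low at interim looks; and the table can falsely reassure if people who worsen stop responding. It should carry a note on the last two limits.

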### Statistical Analysis

Analysis of the primary and secondary outcome measure data will be carried out by the trial statistician, who will remain blind to arm allocation, using STATA 14.

In a RE-AIM study, all outcomes are considered to address important facets of a public health intervention. Therefore, we will examine reach (the percentage and representativeness) of participants entering the trial. Exploratory analysis will summarize outcome variables and participant background variables by treatment arms across follow-up time with mean (SD) for normally distributed data, median (interquartile range) for skewed variables, and frequency (percentage) for observed level of categorical variables. The analysis to examine the treatment effect will be performed on an intention-to-treat basis. As the primary outcome WEWBS score will be repeatedly measured at baseline, 3 weeks, and 6 weeks, multilevel modeling will be performed to quantify the treatment effect with participant as a level 2 unit and baseline measurement as a covariate using Stata 14. Missing values will be imputed using a multiple imputation approach under a missing at random assumption. Path analysis will be used to explore changes in perceived emotional social support and empowerment at 3 weeks as potential mediators for treatment effects on mental well-being at 6 weeks, alongside life events, loneliness, having a partner, gender, age, anxiety without depression, and personality dysfunction at baseline as possible moderators for treatment effect. Such information will provide important information to refine both the targeting and content of BWW to optimize its reach and effectiveness.

A detailed statistical analysis plan setting out full details of the proposed analyses will be finalized before the trial database is locked for final analysis. Stata 14 will be used to perform exploratory data analysis and multilevel modeling, Mplus software (Muthen & Muthen, USA) will be used to perform path analysis [36].

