### Outcome Measures

Once consented, participants will be asked to complete self-rated questionnaires to measure well-being, depression, anxiety, work and social adjustment, QOL (for economic analysis), receipt of services (for economic analysis), social support, and personality dysfunction (see Table 1). These will be completed online (through the study website) in approximately 20 to 30 min, with the primary outcome data collected first. All data will be stored on the website and downloaded and anonymized by the clinical trials manager.

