^a^WEMWBS: Warwick-Edinburgh Mental Well-Being Scale.

^b^PHQ-9: 9-item Personal Health Questionnaire.

^c^GAD-7: 7-item Generalized Anxiety Disorder Scale.

^d^WSAS: Work and Social Adjustment Scale.

^e^MOS-SS: 8-item Medical Outcomes Study Social Support Survey.

^f^X: Measures are not collected at this time point.

^g^SAPAS: Standardised Assessment of Personality-Abbreviated Scale.

^h^Brugha Life: 12-item Brugha Inventory of Life Events.

^i^SF-12v2: Medical Outcomes Study Short Form health survey version 2.0.

^j^CSRI: Client Service Receipt Inventory.

To explore the reach, adoption, and implementation arms of the RE-AIM framework, a number of process measures will be recorded as the study progresses:

Live log of services, individuals, groups, and charities that are approached to engage with the study. The networks that surround these and how this may spread will be recorded and used to determine reach and adoption. A network of practice comprising all health care stakeholders will be established to explore implementation pathways.Reach will be further explored using Internet analytic software or to derive anonymous data around hit and bounce rates, pages visited, length of visit, type of geography, and simple demographics to the study website can be recorded, downloaded, and analyzedImplementation will be explored when highlighting the barriers and drivers to reach, effectiveness, and adoption assessed through qualitative work with the services, groups, and individuals engaged through recruitment, as well as an economic evaluation of its costs and cost-effectiveness from personal, social, and health care perspectives. In particular, we will explore how participants utilize BWW in relation to the literature on similar websites offering peer support and information for physical illness and literature on social and organizational aspects of depression and anxiety care.Working with the local Academic Health Science Network to record the take-up by organizations and implementation (number, percentage, and representativeness in East Midlands) of BWW across the East Midlands after the trial has been completed should it prove to be clinically and cost effective.

In terms of socioeconomic inequalities, we will record the following provided such detailed recording of information does not deter participation: postcode, age, gender, ethnicity marital status, highest level of education, and employment.

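### The exploratory mediation analysis needs the change in social support at 3 weeks, but the schedule collects the social support scale at baseline only

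*Protocol article*

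**What the plan says.** The Statistical Analysis section commits to a mediation model: "Path analysis will be used to explore changes in perceived emotional social support and empowerment at 3 weeks as potential mediators". The outcome of that model is the well-being score at the 6-week wave. The same sentence adds the moderators, "alongside life events, loneliness, having a partner, gender, age, anxiety without depression, and personality dysfunction at baseline as possible moderators for treatment effect".

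Under Secondary Outcomes Measures, the candidate mediators of the effect on well-being "might be the emotional and informational support subscales of the MOS-SS". The entry for that scale gives baseline as its only time of completion. The entries for the GAD-7, PHQ-9 and WSAS each go on to list 3, 6, 12 and 26 weeks. In Table 1 the MOS-SS row reads Website at baseline and X at all four later waves, and the footnote explains: "X: Measures are not collected at this time point".

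The same section raises a further possibility, an interaction between life events at baseline and "greater perceived emotional support from BWW at 3 months and on mental well-being at 6 months".

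The Outcome Measures section describes "self-rated questionnaires to measure well-being, depression, anxiety, work and social adjustment, QOL (for economic analysis), receipt of services (for economic analysis), social support, and personality"; the last item refers to the SAPAS. Neither empowerment nor loneliness is in that list or in Table 1.

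**The concern.** A mediator has to be measured after randomisation, because the model asks whether treatment moves it and whether that movement carries through to the outcome. With the MOS-SS taken only before randomisation, there is nothing for treatment to move.

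This matters beyond tidiness. The Objectives section names quantitative examination of mediators among the ways to learn how the interventions may work. The Background presents BWW as built on a social support model, and the Strengths section counts the moderator and mediator work as a gain of the design. The Statistical Analysis section expects the results to guide the targeting and content of BWW. An analysis plan finalised before database lock can change the model, but it cannot supply 3-week responses that nobody was asked to give.

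**Working it through.** No power or sample size figure enters this point. The check compares each variable in the path model with the measurement schedule.

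**Step 1. Follow-up waves per measure, counted from Table 1 (3, 6, 12 and 26 weeks).**

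| Measure | Collected at 3 weeks | Follow-up waves |
|---|---|---|
| WEMWBS, PHQ-9, GAD-7, WSAS | yes | 4 each |
| SF-12v2, CSRI | no | 1 each (26 weeks, interview) |
| MOS-SS, SAPAS, Brugha life events | no | 0 each |

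Baseline-only collection suits the SAPAS and the life events inventory, which serve as baseline moderators. It does not suit the MOS-SS, which is assigned a mediator role.

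**Step 2. Variables in the path model against their source.**

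| Variable | Role | Needed at | Source in the article |
|---|---|---|---|
| Well-being | outcome | 6 weeks | WEMWBS, collected |
| Perceived emotional support | mediator (change) | baseline and 3 weeks | MOS-SS, baseline only |
| Empowerment | mediator (change) | baseline and 3 weeks | no instrument named |
| Loneliness | moderator | baseline | no instrument named |
| Life events | moderator | baseline | Brugha inventory |
| Personality dysfunction | moderator | baseline | SAPAS |
| Anxiety without depression | moderator | baseline | PHQ-9 and GAD-7 |
| Age, gender, partner | moderators | baseline | sociodemographic items, including marital status |

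**Step 3. Consequence for the support mediator.** Change = (MOS-SS at 3 weeks) − (MOS-SS at baseline). The first term is scheduled for nobody, so the number of computable change scores is 0 in each arm. Without it, neither the path from treatment to mediator nor the path from mediator to outcome can be fitted, and the indirect effect, which combines the two, is not estimable. The planned multiple imputation does not help: a variable observed in no participant has no data from which to impute it.

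**Step 4. The 3-month/6-month hypothesis.** It needs the MOS-SS at 12 weeks and the WEMWBS at 26 weeks. Table 1 provides the second but not the first, so this hypothesis fails for the same reason.

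**Step 5. Could the table be garbled?** The text entry for the MOS-SS and the table row agree with each other, and the footnote defines X outright. A reading error is not a plausible explanation.

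**Step 6. Substitute data.** The content analysis of messages codes support exchanged within BWW. It has no counterpart in the Moodzone arm and does not record perceived support. Empowerment is a topic in the qualitative interviews with BWW participants only. Neither source gives a mediator measured in both arms.

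**The case against.** The strongest reply is that little of consequence is touched. The wording throughout is exploratory, and the primary WEMWBS comparison, its sample size, the multilevel model and the secondary comparisons between arms do not depend on the MOS-SS at follow-up. That stands, and it limits the weight of the point.

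A second reply is that the article condenses a fuller protocol and its lists are not complete inventories. The list in Outcome Measures leaves out life events although Table 1 schedules them, and Table 1 leaves out the demographic items. This also stands for empowerment and loneliness. A reader might infer that they are never measured, but the article shows only that it names no instrument for them. The reply does not rescue the MOS-SS, whose non-collection after baseline is stated, not merely unmentioned.

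Three other stronger readings are tempting and are not supported:

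- **That missing loneliness data block the mediation analysis.** Loneliness is listed as a baseline moderator. Its absence affects one moderator, and the others have a source.
- **That the two timings contradict each other.** The 3-month/6-month sentence concerns an interaction with life events and longer-term well-being. It can stand beside the 3-week/6-week path as a separate hypothesis.
- **That the whole aim of understanding mechanism is lost.** Moderator analyses, interviews and message coding remain. Only the quantitative mediator part fails.

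**Conclusion.** The point holds as an internal inconsistency. The social-support mediation analysis cannot be run on the schedule as printed, because the mediator has 0 of 4 follow-up measurements and none at the 3 weeks that the model requires. The 3-month/6-month hypothesis cannot be tested either. For empowerment and loneliness the conclusion is weaker: no measure is named in the article, and the full protocol may hold one.

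The conclusion rests on one assumption, that Table 1 and the matching text describe what is actually collected. If the live website already asks the MOS-SS at 3 weeks, the error is in the article's schedule and only the text needs correcting.

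The analysis is exploratory and the trial's main result is not at risk, so this should be fixed but does not threaten the trial. It is time-sensitive, since 3-week data not collected at week 3 cannot be recovered. A reader might apply the plan's 50% loss assumption to predict how many participants would supply a change score under a corrected schedule. The article does not support that step: the 50% belongs to the sample size for the 6-week comparison, no 3-week completion rate is given, and no power for an indirect effect is stated.

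**What to change.** 1. Add the 8-item MOS-SS to the 3-week website questionnaire, after the WEMWBS so that the primary outcome is still completed first. Correct the MOS-SS row of Table 1 and its entry under Secondary Outcomes Measures.
2. Add it at 12 weeks only if the 3-month/6-month hypothesis is kept; otherwise delete that hypothesis.
3. If follow-up is too far advanced for a useful number of 3-week responses, delete the social-support mediation analysis and the matching aim in the Objectives, and leave the moderator and qualitative work in place.
4. Remove empowerment and loneliness from the path model unless the full protocol already names a measure for each. If it does, cite the instruments in the article, with empowerment at baseline and 3 weeks and loneliness at baseline.

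The cost is an amendment and eight more items at one online wave, or at two if the 12-week measurement is added, with slight extra burden on participants. The abstract describes the trial as already being conducted, so anyone past week 3 when the change takes effect cannot contribute to the mediation analysis. The report should say from which date the scale was asked.
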